### Phase two: Online international Delphi survey

A sequential 3-round electronic, international Delphi study will be conducted including key stakeholders (patients/public, healthcare professionals, researchers, and service providers) to produce a preliminary PGP-COS. We will use online SurveyMonkey software to conduct the survey (www.surveymonkey.com). Each round will remain open for 14 days and a reminder email will be sent out four working days before closure. The data from each round will be analysed and presented to participants in the subsequent round. We will assess attrition rates for each round for all stakeholder groups.

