#### Participants

We will invite people from all stakeholder groups, aiming for approximately 40 experts from each stakeholder group (patients, clinicians, researchers, service providers/policy makers) to participate (which will provide 20 people randomised to each scale; see methodological study 2). We will recruit participants for the Delphi survey through professional organisations, electronic discussion lists, and patient organisations. We will also encourage snowball sampling, asking participants to forward the invitation appropriately.

Eligible participants will be: (a) Researchers who are actively involved in research related to PGP/lumbopelvic pain and have at least one peer-reviewed publication on the topic; (b) Clinicians, currently treating patients with PGP (including chiropractors, physiotherapists, osteopaths, orthopaedic surgeons etc.); (c) Patients with PGP; (d) Policy-makers, involved in formulating policies related to the management of musculoskeletal conditions including PGP; and (e) Service providers of services for musculoskeletal conditions including PGP. Participants must be able to read and understand English in order to participate.

#### Round 1

Round 1 will collect demographic data including nationality, age, gender, stakeholder group and profession. Participants will rate the importance of each listed outcome. Outcomes will be rated in each round on a 9-point scale [16] or on a 5-point scale (see methodological study 2 below). Participants will also be given the opportunity to add any additional outcomes not already in the list that they think are important. All outcomes from round 1 will be forwarded to round 2.

#### Round 2

Participants who responded to round 1 will be presented with feedback (descriptive statistics) on their own and others’ scores from round 1 and asked to rescore all outcomes and score new outcomes added in round 1. The reason for providing feedback from the previous round to participants is to increase the degree of consensus [14]. Participants will rate outcomes using the same scale they used in round 1. Outcomes from round 2 will be forwarded to round 3 where 70% or more of participants score the outcome as ‘important’ (7 or more on the 9-point scale, or 4 or more on the 5-point scale), and less than 15% of participants scoring an outcome as ‘not important’ (3 or less on the 9-point scale, or 2 or less on the 5-point scale) (Tables 2 and 3).

**Table 2 Tab2:** The 9-point rating scale

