	9-point scale								
Outcome	Not important			Unsure of importance			Important		
Pain	1	2	3	4	5	6	7	8	9
	○	○	○	○	○	○	○	○	○

**Table 3 Tab3:** The 5-point rating scale

	5-point scale				
Outcome	Not important		Unsure of importance	Important	
Pain	1	2	3	4	5
	○	○	○	○	○

#### Round 3

Round 3 will further prioritise outcomes by rescoring the outcomes based on round 2 feedback. Only participants who completed round 2 will be invited to round 3. Outcomes scored by 70% or more of participants as ‘important’ (7 or more on the 9-point scale, or as 4 or more on the 5-point scale), and less than 15% of participants scoring an outcome as ‘not important’ (3 or less on the 9-point scale, or 2 or less on the 5-point scale) will be included in the preliminary PGP-COS. At the end of the round 3 survey we will also include a question to ask if they would be willing to take part in the face-to-face consensus meeting.

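### Drop-out related to opinion can change the status of outcomes near the 70%/15% limits, mainly by deleting them, and the stated attrition check cannot show it

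*Protocol article*

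**What the plan says.** All places are in the protocol article, under Phase two unless stated otherwise.

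- **Entry to round 2** (Round 2): "Participants who responded to round 1 will be presented with feedback", which covers their own and others' scores.
- **Entry to round 3** (Round 3): "Only participants who completed round 2 will be invited to round 3".
- **After round 1** (Round 1): there is no filter. "All outcomes from round 1 will be forwarded to round 2".
- **Cut after round 2** (Round 2): "Outcomes from round 2 will be forwarded to round 3 where 70% or more of participants score the outcome as" important, provided that fewer than 15% score it as not important.
- **Cut after round 3** (Round 3): the same two limits decide entry to the preliminary core outcome set. The text speaks of "Outcomes scored by 70% or more of participants as" important.
- **Check on drop-out** (opening paragraph of Phase two): "We will assess attrition rates for each round for all stakeholder groups". Nothing further is stated about drop-out, apart from a reminder email in each round and, under Sample size, inviting enough people because response can be low.
- **After the survey** (Phase four): the consensus meeting is presented with the preliminary set. It includes an outcome if at least 70% vote for it and at least one patient representative does so.

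The article does not define the denominator of the percentages. It describes no use of the earlier scores of people who have left, so the natural reading is that the denominator is those who rated in the round concerned.

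**The concern.** A percentage among those who remain can move for two reasons: people change their ratings after feedback, or the people who held one view leave. The stated plan does not separate the two. Feedback shows participants where they stand against the rest, so drop-out linked to holding a minority view is plausible, although the article neither assumes nor excludes it.

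An attrition rate counts how many people left. It says nothing about how they had rated. Rates by stakeholder group would show that one group had shrunk more than another, but not what that did to the outcome list, and they would not show selective leaving within a group.

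The two directions of error are not equally serious. An outcome that fails at round 2 or round 3 is not rated again, and no way to recover it is described. An outcome wrongly forwarded at round 2 meets the rule again at round 3 and then the consensus vote.

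**Working it through.** **Inputs from the article.** About 40 people per stakeholder group and four groups, so 4 × 40 = 160. The stated split over the two rating scales reproduces: 40 / 2 = 20 per scale in each group. The limits are at least 70% important and below 15% not important. No attrition rate is given, and the sample size is stated not to rest on a power calculation. All starting shares and retention patterns below are therefore assumptions, with every individual rating held fixed.

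**Step 1. How few leavers suffice if all hold one view.** This is the most extreme pattern and gives the smallest number needed.

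| Share before | Who leaves | Share after | Status |
|---|---|---|---|
| 115/160 = 71.9% | 11 important raters (6.9% of 160) | 104/149 = 69.8% | deleted |
| 120/160 = 75.0% | 27 important raters (16.9%) | 93/133 = 69.9% | deleted |
| 128/160 = 80.0% | 54 important raters (33.8%) | 74/106 = 69.8% | deleted |
| 104/160 = 65.0% | 12 other raters (7.5%) | 104/148 = 70.3% | reaches 70% |
| 96/160 = 60.0% | 23 other raters (14.4%) | 96/137 = 70.1% | reaches 70% |

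**Step 2. Both kinds of rater leave, at different rates.** Let p be the starting share, a the drop-out among important raters and b the drop-out among the others. Then

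share after = p(1 − a) / [p(1 − a) + (1 − p)(1 − b)].

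- p = 75%, a = 40%, b = 20%: 0.450 / 0.650 = 69.2%, deleted (overall attrition 35%).
- p = 75%, a = 30%, b = 10%: 0.525 / 0.750 = 70.0%, still passes.
- p = 65%, a = 10%, b = 30%: 0.585 / 0.830 = 70.5%, reaches 70% (overall 17%).
- p = 60%, a = 10%, b = 40%: 0.540 / 0.780 = 69.2%, does not reach 70%.
- a = b: the expected share stays at p.

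In whole numbers:

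- Deletion: 116/160 = 72.5%; 80 of the 116 and 36 of the other 44 return; 80/116 = 69.0%; attrition 44/160 = 27.5%.
- Forwarding: 104/160 = 65.0%; 88 of the 104 and 37 of the other 56 return; 88/125 = 70.4%; attrition 35/160 = 21.9%.

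Selective drop-out therefore matters for outcomes within roughly 5 points of 70%. Further away, it must be heavy or strongly one-sided.

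**Step 3. Whether the attrition rate would show it.** Let every group fall from 40 to 30, which is 25% attrition everywhere.

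- 26/40 = 65.0% becomes 23/30 = 76.7% if 3 important and 7 other raters leave.
- 30/40 = 75.0% becomes 20/30 = 66.7% if 10 important raters leave.

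The reported attrition table is identical in both cases, and the decisions go opposite ways.

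**Step 4. The 15% limit and the group mix.**

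- 22/160 = 13.8% not important passes. After 20 other raters leave, 22/140 = 15.7% fails.
- Suppose patients rate an outcome important at 90% and the rest at 65%. The panel share is (36 + 78)/160 = 71.3%. If 40% of patients alone leave, it is (21.6 + 78)/144 = 69.2%. The unequal attrition would be seen here, but not its effect on the list.

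**Step 5. Whether the proposed check would show it.** With last ratings carried forward, the two whole-number examples return to (80 + 36)/160 = 72.5% and (88 + 16)/160 = 65.0%. Both changed decisions are exposed.

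**The case against.** The strongest reply is that this is largely silence in a condensed article. Comparing leavers with stayers and running sensitivity analyses often belong in a fuller plan, and the article does not say that attrition rates are the sole check. The illustrations also sit close to the line. One more non-supporter returning gives 88/126 = 69.8%, and four more supporters returning give 84/120 = 70.0%. Ratings are frozen although the rounds exist to let people rescore. People leave the whole survey and not single items, and nothing in the article points to strong drop-out linked to opinion.

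Much of this stands. It limits the point to outcomes near the limits and to an assumed mechanism. It does not remove it, because the entry rule, the cuts and the attrition check are all stated, and the one check named cannot detect the problem.

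Three stronger readings are tempting, and the article does not support them:

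- **Drop-out alone can create consensus.** A reader might infer this from the 65% example. Round 1 applies no threshold, so passing 70% at round 2 only forwards the outcome. It must then pass round 3 and the consensus vote. Loss between rounds 2 and 3 cannot revive an outcome already dropped.
- **Partial round 2 responders help make the cut and are then shut out.** The wording changes from responding to round 1 to completing round 2, but neither term is defined, and nothing says that incomplete round 2 answers count.
- **Excluding people who missed round 2 is itself an error.** With "Each round will remain open for 14 days" and a panel that includes pregnant women, a short absence can end participation. Yet round 3 is rescoring on round 2 feedback, so admitting only round 2 completers is a coherent choice for a sequential Delphi.

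**Conclusion.** The point holds in limited form and should be acted on. The stated check cannot separate growing agreement from selective departure. With no rating changed, outcomes within roughly 5 points of 70%, or near the 15% limit, can change status: 11 leavers out of 160 are enough at 71.9%, and 27 at 75%, if all had rated the outcome important. False deletion is the main harm, because no route back is described; false forwarding is checked twice more.

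The conclusion rests on three assumptions: percentages are taken among current-round raters, drop-out is related to opinion or stakeholder group, and the panel is near 160. If drop-out is unrelated to opinion, the expected share does not move.

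**What to change.** Add to Phase two, before the round 2 cut is made:

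1. At the round 2 and round 3 cuts, tabulate the previous-round ratings of leavers and stayers for each outcome, within stakeholder group, next to the attrition rates.
2. As a sensitivity analysis, re-apply the 70%/15% rule with each leaver's last recorded rating carried forward, only for outcomes that person rated. Take any outcome whose status changes to the consensus meeting, flagged as such.

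The primary rule stays as it is. Carried-forward scores predate the feedback and assume that no leaver would have changed their mind, so they are fit for a sensitivity analysis only.

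The cost is some protocol wording and one extra table. Participants are shown their own earlier scores, so ratings must already be linked to individuals. A few more outcomes may reach the meeting.

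Re-inviting people who missed round 2 is an optional design choice and not part of this fix. It would bring in raters with no round 2 score and, for outcomes added in round 1, no earlier score at all.

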#### Methodological study 2: Different scales to rate outcome importance

The 9-point scale, whereby a score of 1–3 means limited importance, 4–6 means maybe important but not critical, and 7–9 means critically important, is commonly used in Delphi surveys for COS development [14] and is based on the recommendations of the Grading of Recommendations Assessment, Development and Evaluation (GRADE) working group to assess the importance of evidence. However, other scales have been used [24, 25], and comments from some participants in round 1 of an in-progress recent Delphi survey described the 9-points scale as somewhat confusing and that a smaller scale might have been more user friendly [26]. Currently, no studies have examined the impact of using different likert scales on the final COS. We aim to compare the use of a 9-point scale (Table 2) versus a 5-point scale (Table 3). Participants of the Delphi survey, when clicking on the link to the survey, will be randomised to completing the survey using either a 9-point or 5-point scale. Specific software has been developed to enable this [27]. We will compare the two groups, with regards to the following outcomes: (a) the proportion of outcomes rated as ‘important’ (7 or above on 9-point scale, and 4 or 5 on 5-point scale) in each round and any differences between the scales, in the outcomes that are included in the preliminary COS after round 3. We will use z-scores to test the differences in proportions between the groups, and calculate overall mean scale differences on each outcome to assess differences. Recognising that differences can occur due to chance, and allowing for a 20% possibility of this, we would anticipate balance between the groups due to random allocation and thus similarity in overall scale scores for each outcome by population group. We will also ask participants to rate the ‘ease of use’ of the rating scale to assess utility.

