## Objectives

To collate a list of reported outcomes from a systematic review of the literature of studies on PGP and from patient interviews for use in a Delphi survey;To develop consensus on a preliminary PGP-COS, using the list of outcomes from Objective 1, via a 3-round international electronic Delphi survey;To synthesise the evidence on the available outcome measurement instruments for measuring the construct outcomes (e.g. pain) in the preliminary PGP-COS;Using the preliminary PGP-COS (Objective 2), develop a final PGP-COS for use in all future studies on PGP, and in clinical practice, including how to measure the outcomes in the COS, via an international face-to-face consensus meeting with key stakeholders;To disseminate and promote the implementation of the COS to key stakeholders internationally;

In addition, we have two methodological objectives:6.To determine if including patient interviews in addition to a systematic review to identify the initial list of outcomes influences the final COS;7.To evaluate any differences in using a 9-point versus a 5-point rating scale in the Delphi survey, in terms of its impact on the number of ‘important’ ratings received for each outcome in each round of the survey and on the final PGP-COS.

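### The comparison of which outcomes each rating scale puts into the preliminary COS has no chance reference, and some disagreement is likely by chance unless few outcomes have support near 70%

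*Protocol article*

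**What the plan says.** Objective 7 asks whether the choice of scale matters "in terms of its impact on the number of ‘important’ ratings received for each outcome in each round of the survey and on the final" core outcome set. The section on methodological study 2 turns this into two comparisons: the proportion of outcomes rated important in each round, and "any differences between the scales, in the outcomes that are included in the preliminary COS after round 3".

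The Round 3 section defines inclusion by two conditions that must both hold. The first begins "Outcomes scored by 70% or more of participants as" important, meaning 7 or more on the 9-point scale or 4 or more on the 5-point scale. The second requires "less than 15% of participants scoring an outcome as" not important. Round 2 uses the same rule to decide what goes forward, without saying whether it is applied per scale or to both scales together.

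For numbers, the Participants section seeks roughly 40 people in each of four stakeholder groups and says of that figure: "which will provide 20 people randomised to each scale; see methodological study 2".

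For inference, the plan states: "We will use z-scores to test the differences in proportions between the groups". It adds mean scale differences per outcome. It recognises that chance produces differences and mentions a 20% allowance, which it links to similarity of overall scale scores for each outcome by population group. It gives no amount of list disagreement expected by chance, no agreement statistic and no rule for ascribing a list difference to the scale.

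**The concern.** The list comparison is the part of study 2 that speaks most directly to whether the scale changes the core outcome set. To make it, the inclusion rule must be applied within each arm and the two lists set side by side. Each list is then a thresholded estimate from a separate random part of the panel. A small sampling difference on either side of 70% becomes a categorical difference, included or not included.

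The article says that no study has yet examined the effect of the scale on the final set, so later developers may rely on this result. If outcomes found on one list and not the other are reported without a reference, a reader cannot tell them from what two random halves of one panel would produce on the same scale. The concern is limited to the list comparison. It does not extend to the z-tests or the mean scores.

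**Working it through.** **Inputs from the article**
- Raters per arm: 40 / 2 = 20 per stakeholder group, which reproduces the article's figure. Four groups give 4 × 20 = 80 per scale. The 80 is derived, and it is a round 1 ceiling because only round 2 completers are invited to round 3.
- Inclusion with 80 raters: at least 0.70 × 80 = 56 rate the outcome important. Since 0.15 × 80 = 12, at most 11 rate it not important.
- Not given: the number of outcomes K, their true support, the attrition rate, and whether the round 2 filter is pooled.

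**One outcome, no scale effect.** Let q be the chance that an outcome with true important share p passes the 70% limb in one arm: q = P(Bin(80, p) ≥ 56). The two arms disagree with probability 2q(1 − q).

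| True share p | q | 2q(1 − q), 80 per arm | 60 per arm |
|---|---|---|---|
| 0.65 | 0.207 | 0.33 | 0.38 |
| 0.70 | 0.555 | 0.49 | 0.49 |
| 0.75 | 0.876 | 0.22 | 0.25 |
| 0.80 | 0.989 | 0.02 | 0.04 |

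Adding the 15% limb, with one third of the remaining ratings assumed not important, changes little: 0.32, 0.50, 0.24 and 0.03. As a plain check, the standard error of the between-arm difference at p = 0.70 is √(2 × 0.7 × 0.3 / 80) = 0.072, so chance gaps of about 7 percentage points are ordinary.

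**Several borderline outcomes.** At about 0.50 each and treated as independent, the chance of at least one disagreement is 1 − 0.5² = 0.75 for two outcomes, 1 − 0.5³ = 0.88 for three and 1 − 0.5⁵ = 0.97 for five.

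**A whole list, no scale effect, round 2 filter pooled.** These are simulated chances of at least one discordant outcome and depend on the assumptions shown.
- A: true shares uniform on 30–95% or 50–95%; one third of the remainder not important; rater correlation 0.2; 80 per arm in both rounds.
- B: as A, with 60 per arm in round 2 and 50 in round 3.
- C: true shares uniform on 40–95%, 50–95% or 60–98%; 40% of the remainder not important; 160 raters in total throughout, or 140 then 120; with and without a rater leniency effect.

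| K | A | B | C |
|---|---|---|---|
| 10 | 0.34–0.46 | 0.42–0.52 | – |
| 20 | 0.58–0.69 | 0.63–0.77 | 0.69–0.86 |
| 30 | 0.72–0.86 | 0.80–0.90 | 0.84–0.96 |
| 50 | 0.90–0.96 | 0.93–0.98 | 0.94–0.99 |

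If each arm is cut separately with no pooled filter, 80 per arm and the shares of A, the chance is 0.58–0.76 for 10 outcomes, 0.85–0.94 for 20 and 0.94–0.99 for 30.

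**When no outcome is near the cut.** With 80 per arm, one third of the remainder not important, and all shares at least 0.80 or split between at most 0.57 and at least 0.82, the chance is 0.01–0.10 for 10 to 30 outcomes and 0.07–0.22 for 50 to 80. With 50 per arm the same patterns give 0.06–0.28 and 0.29–0.59.

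**Do the z-tests settle it?** With lists cut separately, only about 12–20% of chance-discordant outcomes also differ at two-sided 0.05 on the z-test of round 3 proportions. Most such list differences are therefore threshold noise. The z-tests still give no expected number of discordant outcomes.

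**The case against.** The strongest reply is that the plan contains no rule making one discordant outcome a scale effect. That is correct. A reader might infer such a rule from the wording of the list comparison, but the article only says the groups will be compared on it, and a descriptive comparison has no false-positive rate until a decision is attached.

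Second, the same section acknowledges chance and plans z-tests and mean differences, which can be read outcome by outcome beside the lists. This helps in part: most chance-discordant outcomes would show no clear difference in proportions. It does not say how much disagreement between the lists is more than chance.

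Third, a reader might set the list-wide chance against the 20% allowance and conclude that the allowance is exceeded several-fold. The document does not support that, because the 20% concerns scale scores for each outcome, not at least one disagreement across a list. Per outcome, the average chance of discordance is lower: at K = 30 with 80 per arm (shares as in A), 1.3–1.8 discordant outcomes with a pooled filter is 1.3/30 to 1.8/30, about 4–6%. With separate cuts, 2.5–4 of 30 is about 8–13%.

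Fourth, feedback is meant to increase consensus and may move support away from 70%. The simulations do not model such convergence, and uniform shares ensure that some outcomes lie near the cut.

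Fifth, an agreement statistic for an embedded comparison might be left to a fuller plan. Here, though, the article names both the comparison and its statistics, and those statistics do not fit the comparison.

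**Conclusion.** The point stands in a limited form. As written, the list comparison cannot separate a scale effect from threshold noise, because it has no chance reference. Near 70% support the noise is large: about one chance in two per outcome at 70%, one in three at 65% and one in five at 75%.

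How often at least one outcome differs across a whole list rests on inputs the article does not give. Under spread shares and a pooled round 2 filter it is roughly 0.35–0.6 for 10 outcomes, 0.6–0.9 for 20 and 0.7–0.95 for 30. It is under 0.25 with 80 raters per arm when no outcome lies near the cut. A reader might go further and say that a difference will almost always appear. That holds only for long lists with several borderline outcomes and cannot be derived from the document.

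The weakness affects what can be concluded for objective 7. The text should be changed, since a better comparison is available from the same data.

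**What to change.** State that the round 2 filter is pooled over both scales, so that both arms rate the same outcomes in round 3. Then:

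1. Apply the 70%/15% rule within each arm to those outcomes and count the discordant ones.
2. Permute scale labels between participants within stakeholder group, keeping each participant's important / unsure / not important classifications together. Recompute both lists and the count each time.
3. Attribute list differences to the scale only if the observed count exceeds the 95th percentile of the permutation distribution.
4. For each discordant outcome, report the between-arm difference in percentage rating it important, with its confidence interval.

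The permutation has a limit that should be written down. If the round 2 filter or the feedback is specific to each arm, participants in an arm influence each other or rate a different set, and the permutation is not exact in the later rounds. In that case, apply it to the round 1 ratings, which precede any feedback, and report later list differences descriptively with the confidence intervals.

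The cost is a sentence or two of analysis text and a short script on data already collected. The downside is that a few discordant outcomes can no longer be presented as a scale effect.

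### Methodological study 2 compares mean scores between a 1–9 arm and a 1–5 arm without a common metric, so the mean differences mainly reflect scale length

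*Protocol article*

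**What the plan says.** The section on methodological study 2 sets out the comparison: "We aim to compare the use of a 9-point scale (Table 2) versus a 5-point scale (Table 3"). Participants "will be randomised to completing the survey using either a 9-point or 5-point scale", and under Phase two, Round 2, the scale is fixed from then on: "Participants will rate outcomes using the same scale they used in round 1". No one therefore scores on both scales.

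Tables 2 and 3 number the scales 1–9 and 1–5. On the first, 1–3 is not important, 4–6 unsure and 7–9 important. On the second, the bands are 1–2, 3 and 4–5.

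The ratings of the two arms are to be compared in these ways:

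- On the proportion rated 'important', with a cut-point for each scale ("7 or above on 9-point scale, and 4 or 5 on 5-point scale"), and on which outcomes reach the preliminary core outcome set. For the proportions: "We will use z-scores to test the differences in proportions between the groups".
- On mean scores: the plan will "calculate overall mean scale differences on each outcome to assess differences". Because allocation is random, it anticipates "similarity in overall scale scores for each outcome by population group".

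The article mentions no rescaling, standardising or mapping of scores before means are compared. The z-scores are tied to the proportions only.

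**The concern.** Randomisation balances the opinions of the two arms. It does not make scores alike when one arm can score up to 9 and the other only up to 5. The step from random allocation to similar scale scores therefore does not follow, and a benchmark built on it misleads in both directions:

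- Arms that agree look different. The gap also grows with the importance of the outcome, so comparing gaps across outcomes does not rescue the analysis.
- Arms that disagree can look alike. A mean of 4.5 in both arms would count as perfect similarity, yet 4.5 lies in the 'unsure' band of Table 2 and in the 'important' band of Table 3.

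At stake is the interpretation of one supplementary analysis in a study that the article presents as the first to examine the effect of the rating scale.

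**Working it through.** **Inputs from the article.** Scale ranges 1–9 and 1–5 and their bands (Tables 2 and 3); cut-points for 'important' of 7 and 4, and for 'not important' of 3 and 2 (Rounds 2 and 3); about 40 participants per stakeholder group (Sample size).

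**The plan's own figure.** 40/2 = 20 per scale in each stakeholder group, as stated. Over four groups, 4 × 40/2 = 80 per scale. The article gives no standard deviation, effect size or significance level for the mean comparison. The size of the artefact does not depend on the number of participants.

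**Step 1: identical opinions, linear map (assumption).** Let u be an opinion's relative position between the bottom (0) and the top (1) of the scale.

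- 9-point score = 1 + 8u
- 5-point score = 1 + 4u
- difference = 4u, which equals the 5-point score minus 1

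| u | 5-point | 9-point | Difference |
|---|---|---|---|
| 0 | 1 | 1 | 0 |
| 0.25 | 2 | 3 | 1 |
| 0.50 | 3 | 5 | 2 |
| 0.75 | 4 | 7 | 3 |
| 1 | 5 | 9 | 4 |

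**Step 2: the same check from the bands alone.** The midpoints of the three bands are 2, 5 and 8 in Table 2, and 1.5, 3 and 4.5 in Table 3. The gaps are 0.5, 2.0 and 3.5, which is the same pattern.

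**Step 3: does it depend on the linear map?** One common distribution of opinions was simulated and scored on both scales. The assumptions were five Beta shapes, from very low to high importance, and three response rules (equal-width bins, nearest anchor, bins aligned with the bands).

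| Outcome | Unscaled mean difference, 9-point minus 5-point |
|---|---|
| Rated very low | 0.26 to 0.44 |
| Rated lowish | 1.19 to 1.34 |
| Mid-scale | 2.00 |
| Above mid-scale | 2.67 to 2.81 |
| High importance | 3.18 to 3.38 |

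The artefact persists under every response rule and is small only at the bottom.

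**Step 4: rescaling.** With (score − 1)/8 and (score − 1)/4, both scores in Step 1 reduce to u, so the difference is 0. The article's cut-points then coincide:

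- 'important': (7 − 1)/8 = (4 − 1)/4 = 0.75
- 'not important': (3 − 1)/8 = (2 − 1)/4 = 0.25

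In the simulation, the differences left after rescaling lie between −0.035 and +0.024 on the 0–1 range. The example of a mean of 4.5 in both arms becomes 3.5/8 = 0.44 against 3.5/4 = 0.88, so the disagreement is visible.

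**The case against.** The strongest reply is that the article nowhere says the scores are unscaled. It is a condensed account, and a rescaling formula could sit in a fuller plan. The expectation of similar scores could even be read as presuming a common metric. It is true that the lack of rescaling is inferred from silence. But the article does name the statistic and the result it expects, and it derives that result from random allocation alone. That inference is wrong unless a common metric is stated.

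Four further points stand and limit the concern:

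- **Reach within the study.** A reader might infer that objective 7 as a whole is compromised. The article does not support this. Objective 7 is framed by the number of 'important' ratings and the effect on the final core outcome set. Both rest on cut-points specific to each scale, so the numerical range does not distort them.
- **Every outcome.** A reader might infer that the arms must differ on all outcomes. The difference is 4u, which is zero at the bottom and small for outcomes rated very low.
- **Significance.** A reader might infer that the arms would be declared significantly different. With assumed standard deviations of 2 and 1, a 3-point gap has standard error √(4/20 + 1/20) = 0.50 and z = 6 with 20 per arm, or √(4/80 + 1/80) = 0.25 and z = 12 with 80. But the plan specifies no test of the means, and neither the standard deviations nor full retention comes from the article.
- **The remedy.** Linear rescaling assumes equally spaced responses, while the bands split 3/3/3 and 2/1/2. If a two-sided 5% test were applied to the rescaled means, identical opinions would still be rejected in up to 13% of cases with 20 per arm and 36% with 80, in the worst simulated settings. Most settings gave 5–6% with 20 per arm. What remains comes from the response format and is part of the scale effect the study wants to learn about.

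**Conclusion.** The point holds for the mean comparison only, and it is moderate. Taken as written, arms with identical opinions would differ by about 2 points at mid-scale, 3 at the 'important' cut and 4 at the top, falling to zero only for outcomes rated at the very bottom. Those figures rest on the scale ranges in Tables 2 and 3 and on linear responding; the band midpoints and the simulation give the same pattern. The statement that random allocation implies similar scale scores needs correcting whatever the data show.

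The comparison of proportions rated 'important', the rules for carrying outcomes into round 3 and into the preliminary core outcome set, and the consensus vote do not use the between-arm means. Nothing here threatens the core outcome set.

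**What to change.** In the section on methodological study 2, add a sentence on these lines:

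> *Before means are compared, each rating is rescaled to 0–1, as (score − 1)/8 in the 9-point arm and (score − 1)/4 in the 5-point arm; the difference in rescaled means is reported with a 95% confidence interval for each outcome and stakeholder group.*

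Reword the expected similarity so that it refers to rescaled scores. Add that linear rescaling assumes equally spaced responses, and that any remaining difference due to response format is read as part of the scale effect.

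The alternative is to drop the mean comparison and rely on the proportions rated 'important'.

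The cost is a sentence or two of text and one line of code. Data collection, randomisation and sample size do not change, and the rescaling can be applied to the collected ratings at analysis.
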